### Training facilitators

For it to make sense to compare and differentiate between the two active music interventions, according to Waltz [34] it is necessary to describe them in detail and train facilitators of the intervention thoroughly. The MUFASA group worked towards making the level of “essential and unique” obviously different while elements of both “essential” and especially “compatible” and “proscribed” are more alike. The facilitators were trained separately and their training including reading an elaborate intervention guide, reading relevant literature, and trying out the interventions in a role model teaching format where co-trainees and voluntary music therapy students roleplayed different types of family dyads with children in the age of 7–8. Based on short descriptions of the dyads, the facilitator-trainee planned a session with activities, tried it out in the role-model format and received feedback from peers as well as members from the MUFASA group. The group discussions were also used to clarify and edit elements of the written treatment guideline. The trainees only had access to one intervention guideline to avoid confusion about differences and similarities and to not be influenced by the other guideline.

### Concerts for families

The primary goal for family-concerts is to provide families with shared and meaningful experiences to strengthen family well-being. The criteria for which family concerts families should be offered to participate in are developed together with Musikkens Hus in Aalborg and Musikhuset in Aarhus, respectively, which also have many years of successful experience in offering activities for families with school children. Due to Covid19, it was not possible during the pilot study to choose or have families participate in family concerts. However, based on discussion with Musikkens Hus and Musikhuset the following criteria were chosen for the main study; concerts aimed at families in their description and/or title including both classical music and rhythmical music in both small and larger ensembles. The rationale behind these criteria is that included concerts should portray or represent regular possibilities in everyday life for families with children aged 7–9.

### Assessment of treatment fidelity

As mentioned, it is necessary to monitor whether the planned intervention is also the intervention delivered in the study [34]. Therefore, both facilitator as well as independent raters in the MUFASA project are to evaluate if it is possible to follow the intervention guide. Partly to know more about what is happening during the sessions so that we can understand the outcomes, but also for us to be able to validate the interventions. Below you can read the preliminary forms that we expect will be filled in partly after each session by the therapist and by independent raters who will watch random videos from the sessions. The treatment fidelity forms are strongly linked to the intervention guides and should be familiar to the facilitator.

### Power calculation and sample size

As no similar studies have been carried out previously, the basis for this calculation is sparse. There is no consensus on the minimal clinical difference in measures of parent-stress, child well-being, and parent–child interaction when participating in music activities. Overall, effect sizes appear to range from medium to large, e.g., between d = 0.57 and 1.60, and to be evident in similar studies where families participate in music and music therapy activities [43, 44].

The power calculation for the primary outcome measure APCI is based on a comparison between music therapy with vulnerable families and music therapy with more well-off families. For 32 randomised parent–child pairs, 90% power will be achieved for effect sizes between 0.57 and 1.6. Assuming drop-out does not exceed 10%, the aim is to recruit approximately 40 participants in total in addition to the pilot families.

### Outcomes measures

The study will use assessments by blinded clinicians as well as reports by parents/guardians. The music therapy activities will take place from 18 to 22 months and will be supported by an experienced family supervisor. The family concerts will take place 18–24 month, where the families' participation is closely followed by the project manager also through questionnaires. Measures of mental health and family interaction will be taken before and after participation in music and music therapy activities and subsequently one year after (months 18, 22 and 34) three times in total. The APCI is the primary outcome, and the PSS and the SDQ the secondary outcome measures. Besides these standardized questionnaires, the study will also collect data about family's everyday participation in other cultural or music activities and whether there is any shared music activates besides the activities offered in the MUFASA study.

Assessment of Parent Child Interaction (APCI) combines structure with flexibility and measures the actual interaction between parent and child. It is an observational and improvisational music therapy assessment tool with validity and reliability evidence [45, 46] that assesses the dyads of parent and child (5–12 years). The family sees the music therapist for 2 × 25 min with a week in between the two sessions, during which they do various exercises together and their interaction is videorecorded. The tool is thus based on video analysis and produces information about parent–child interaction and parenting skills including degree of mutual attunement, nonverbal communication, indication of attachment and degree of emotional parent response [47, 48].

Parental Stress Scale (PSS) is an internationally used questionnaire with evidence of validity and reliability [38] that assesses positive and negative aspects of parenting, including perceived stress, positive emotions, or experiences with parenting (including emotional gains, enrichment, and personal development), and negative aspects of parenting, such as guilt or lifestyle limitations. The positive and negative aspects of parenting are elucidated through 18 questions resulting in an overall parenting stress score [49].

The Strengths and Difficulties Questionnaire (SDQ) is a short questionnaire with evidence of validity and reliability [39] that assess children and young people's psychological well-being and functioning. It has been tested worldwide and translated into over 70 different languages and dialects. The SDQ has 25 questions and five additional questions asking the respondent (parents, when the child is under 11) to rate the duration of difficulties and their impact on everyday life, the latter being expressed in a strain score. The 25 questions have five questions on strengths and 20 questions on difficulties [50].

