**Methods:**

The study is a controlled effect study where 40 family dyads from Aalborg and Aarhus are randomized into 4 different groups including music therapy activities, community music, family concerts and a control group. Measurements of family interaction (Assessment of Parent Child Interaction, APCI) and mental health (Parental Stress Scale, PSS, and the Strengths and Difficulties Questionnaire, SDQ) will be made at baseline/pre intervention, at post intervention and a follow-up measurement 12 month after baseline (month 1, 3 and 12) 3 times in total. Furthermore, data about the family dyad’s regular participation in music events as part of every-day life at the same measure points (month 1, 3 and 12). Since this is a planned prospective study, results are not yet available, but clinical experience from a feasibility study in 2021 were promising and expected challenges and changes are discussed in the article.

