### Statistical analysis

To examine the effect, repeated measures between groups (split-plot factorial) are used, where families are randomly assigned to participate in 4 different activities. Furthermore, adjusted linear mixed-effects models (LMEMs) are used to account for random effects in relation to participation in other cultural activities over the 3 years of the study. Measures are taken before music activities, shortly after and long after families have participated in music activities (see Fig. 1). To examine the relationship between parent-stress, child well-being and parent–child interaction and cultural participation, extended correlation analyses are also used, focusing on change over time and with time as a factor. A Mauchly test will be calculated for each variable to ensure the assumption of sphericity. Likewise, a Box's test will be performed to ensure covariance (equality of covariance). An alpha level of 0.05 is planned to be used for all statistical tests. If necessary, missing observations can be estimated and degrees of freedom should be adjusted downwards accordingly. Effect sizes are measured by calculating Cohen's d using the average of the standard deviations from pre- and post-measurements in both groups and conditions and adjusting for the correlation between the three measurements.

Different correlation measures will be used in this study to verify the degree of association between the APCI measures with that of the PSS and SDQ questionnaires in each of the different interventions, considering the different timepoints. These correlations are important because the constructs of each outcome measure are not the same, but they measure related constructs that may be associated in some way.

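### The protocol gives two assessment timetables that cannot be reconciled, and the month-22 'after' visit falls before the stated concert window closes

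*Protocol article*

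**What the plan says.** The Methods part of the Abstract plans a baseline measure, a post-intervention measure and "a follow-up measurement 12 month after baseline (month 1, 3 and 12) 3 times in total". It repeats these months for the data on everyday music participation, collected "at the same measure points (month 1, 3 and 12").

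The Outcomes measures section says that the outcomes "will be taken before and after participation in music and music therapy activities". Its third assessment, the follow-up, comes "subsequently one year after (months 18, 22 and 34) three times in total". The same section sets the activity windows: "The music therapy activities will take place from 18 to 22 months" and "The family concerts will take place 18–24 month". It gives one set of assessment months, with no separate dates for the concert arm. The text states no window for community music.

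The Statistical analysis section describes the timing in words: "Measures are taken before music activities, shortly after and long after families have participated in music activities". It refers to Fig. 1, which is not shown in the text at hand.

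**The concern.** The main analysis is a split-plot repeated-measures comparison of four groups over three time points, and it covers the APCI as primary outcome and the PSS and SDQ as secondary outcomes. Each level of the time factor needs one definition. Here post and follow-up have two definitions each, and follow-up is tied once to baseline and once to the end of participation. A reader of the results could not tell which time point was planned. A visit held at the wrong time cannot be recovered at analysis, least of all for the APCI, which needs two video-recorded sessions a week apart.

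The second issue lies within the later timetable. One 'after' month is given for activities whose stated windows end in different months, so the visit labelled post may not follow the activity in the concert arm.

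**Working it through.** **Inputs.** Abstract: months 1, 3, 12. Outcomes measures: months 18, 22, 34; music therapy 18 to 22; concerts 18 to 24.

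**Step 1. Reproduce each timetable from its own wording.**
- Outcomes measures: music therapy starts at 18 and ends at 22, and one year later is 22 + 12 = 34. The printed months are reproduced, but only for the music therapy window.
- Abstract: month 1 to month 12 is 12 − 1 = 11 months, against the stated 12 months after baseline. This is approximate agreement. Follow-up is taken below as 11 (by subtraction) to 12 (as worded).

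**Step 2. Compare the intervals.**

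| Interval | Abstract | Outcomes measures |
|---|---|---|
| Baseline to post | 3 − 1 = 2 | 22 − 18 = 4 |
| Post to follow-up | 12 − 3 = 9 | 34 − 22 = 12 |
| Baseline to follow-up | 12 − 1 = 11 (12 as worded) | 34 − 18 = 16 |

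**Step 3. Test for a change of origin.** If one list counted participant months and the other project months, the differences would be constant. They are 18 − 1 = 17, 22 − 3 = 19 and 34 − 12 = 22. No single shift fits.

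**Step 4. Compare the follow-up anchors.** On the 18/22/34 calendar, 12 months after baseline is 18 + 12 = month 30. One year after music therapy ends is month 34. The two definitions of follow-up differ by 34 − 30 = 4 months, so the conflict lies in the wording as well as in the month numbers.

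**Step 5. Set the month-22 and month-34 visits against the windows.**
- Month 22 is 22 − 22 = 0 months after the music therapy window ends, and 24 − 22 = 2 months before the concert window ends.
- Month 34 is 34 − 22 = 12 months after the music therapy window ends, and 34 − 24 = 10 months after the concert window ends. One year after the concert window would be 24 + 12 = month 36.

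**Step 6. Can one common calendar remove the difference?** The windows last 4 and 6 months and start together. Any common visit therefore differs by 24 − 22 = 2 months between these two arms in time since the window ended. A post visit at month 24, for example, would fall 2 months after music therapy had ended.

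**The case against.** The contradiction between the two timetables has no good defence. The best one, that they count from different origins, fails at Step 3. Fig. 1 might show arm-specific dates, but it could not make the two sets of stated intervals agree.

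The concert point is more open. Months 18 to 24 may be the period in which concerts were on offer rather than each family's exposure; no number of concerts or attendance dates is given. The visits are tied in words to participation, so a family whose last concert came before month 22 would be measured after its own participation. That all arms share month 22 is inferred from the single list of months. This objection stands, and it makes the point conditional on attendance after month 22.

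A reader might infer more than the text supports:
- **That the four arms are compared at different points.** With a common month 22, all arms are at the same time since baseline. Only time relative to the end of activity differs, and this is shown for concerts against music therapy alone. No window is stated for community music, and none is stated for the control group.
- **That the post comparison is biased against concerts, or misses about a third of their effect.** By month 22, 4 of the 6 months of the window have passed, but that is calendar time, not exposure. The one-third figure needs benefit to accrue linearly and attendance to be spread evenly to month 24; neither is stated. If benefit peaks early or fades once activity stops, measuring while concerts continue could favour concerts.
- **That the two cities would follow different timetables.** Nothing suggests that either would work from the Abstract.

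**Conclusion.** The contradiction on assessment timing is established from the text and rests on no assumption. Post is at 2 or 4 months from baseline, follow-up is at 11 to 12 or 16 months, and the follow-up anchor differs. Because this fixes when the primary outcome is measured, it must be corrected.

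The concert point holds in a limited form. If the listed months apply to the concert arm and some of its families attend after month 22, the month-22 visit is not post-intervention for them, contrary to the Abstract and the Statistical analysis section. Month 34 is then 10 rather than 12 months after the concert window ends. The documents settle neither the direction nor the size of any bias.

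**What to change.** Reconcile the Abstract, the Outcomes measures section and the Statistical analysis section into one visit schedule, counted from baseline, with a single anchor for follow-up. Baseline is the natural origin because the Study design section places it before allocation. Which calendar applies is for the study team.

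For the second visit, either:
- place it after every arm's activity has ended and call it post-intervention; or
- keep the common month-22 visit and, for the concert arm, label and interpret it as time since baseline rather than as post-intervention.

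Neither option equalises time since the end of activity when the windows last 4 and 6 months. In either case, report the remaining difference between arms alongside the results.

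The cost is a text change, which the planned protocol updates could carry. No extra visits are needed; the first option may mean a later post visit for some arms.

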### Data management and storage

As the principal investigator and first author has no active task in assessing, rating, or facilitating intervention in connection with data collection, together with the second author they have shared responsibility to enter, code, anonymize, store and secure data using legal university software and storage with the aim of promoting data quality and accuracy. Furthermore, data monitoring is also handled by PI using closed excel sheets and SPSS docs. All participants are informed about legal GDPR storage of data including anonymization (code for finding individuals are available as long as the study runs and is then deleted) and rights and possibilities to cancel participation. Each participant gives individual consent to publication and different types of usage of video material for research analysis and training purposes.

### Statistical analysis

To examine the effect, repeated measures between groups (split-plot factorial) are used, where families are randomly assigned to participate in 4 different activities. Furthermore, adjusted linear mixed-effects models (LMEMs) are used to account for random effects in relation to participation in other cultural activities over the 3 years of the study. Measures are taken before music activities, shortly after and long after families have participated in music activities (see Fig. 1). To examine the relationship between parent-stress, child well-being and parent–child interaction and cultural participation, extended correlation analyses are also used, focusing on change over time and with time as a factor. A Mauchly test will be calculated for each variable to ensure the assumption of sphericity. Likewise, a Box's test will be performed to ensure covariance (equality of covariance). An alpha level of 0.05 is planned to be used for all statistical tests. If necessary, missing observations can be estimated and degrees of freedom should be adjusted downwards accordingly. Effect sizes are measured by calculating Cohen's d using the average of the standard deviations from pre- and post-measurements in both groups and conditions and adjusting for the correlation between the three measurements.

Different correlation measures will be used in this study to verify the degree of association between the APCI measures with that of the PSS and SDQ questionnaires in each of the different interventions, considering the different timepoints. These correlations are important because the constructs of each outcome measure are not the same, but they measure related constructs that may be associated in some way.

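### The estimate-and-lower-df rule for missing values does not by itself hold the 5% level, and using baseline as an outcome level gives up precision; a baseline-adjusted version of the planned mixed model would address both

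*Protocol article*

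**What the plan says.** The Statistical analysis section of the protocol article opens with the effect analysis: "To examine the effect, repeated measures between groups (split-plot factorial) are used". The repeated factor has three levels, one of them before the intervention: "Measures are taken before music activities, shortly after and long after families have participated in music activities". Baseline APCI is therefore one of the outcome values and not a covariate.

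For incomplete data the rule is: "If necessary, missing observations can be estimated and degrees of freedom should be adjusted downwards accordingly". No method of estimation and no missingness assumption is given.

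Mixed models are planned as well, but for another stated purpose: "adjusted linear mixed-effects models (LMEMs) are used to account for random effects in relation to participation in other cultural activities". The section calls them adjusted without listing covariates. It does not give them the task of handling missing data or adjusting for baseline APCI. The test level is fixed by "An alpha level of 0.05 is planned to be used for all statistical tests".

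**The concern.** Subtracting one degree of freedom per estimated value is the textbook companion of a single fill; it does not describe multiple imputation. It corrects only part of the problem. A mean over nine observed values and one invented value is still treated as a mean of ten, so its standard error is too small. Missing values are to be expected here, since the article allows for dropout of up to 10% and follow-up runs to 12 months after baseline.

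The second issue is precision. With about 10 dyads per arm the trial has little to spare. Comparing raw changes from baseline, as the group-by-time test does, uses the baseline less efficiently than regression adjustment.

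**Working it through.** **Inputs**
- 40 dyads in four groups (Abstract; Power calculation and sample size): 40/4 = 10 per arm, taking the arms as equal.
- Dropout not above 10% (same section): 1 of 10 per arm. A loss of 2 of 10 exceeds that ceiling. It is shown because it is the loss that would take 40 dyads to the 32 of the power statement (1 − 32/40 = 20%).
- Level 0.05, taken as two-sided.
- Correlation r between baseline and later APCI: not given. Assumed 0.5, 0.7 and 0.9, with equal variances.

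The article gives no figure for the error rate or precision of this analysis, so there is none to reproduce. Its power statement is a separate matter and is not relied on here.

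**Step 1: what the df reduction corrects.** Take one visit, two arms of n = 10, and k missing per arm, each filled with its arm mean. Filled values add nothing to the residual sum of squares, so reducing df from 2n − 2 to 2n − 2 − 2k gives the right residual variance s². The analysis then uses a standard error of s√(2/n), while the correct one is s√(2/(n − k)). The true rejection rate is

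2·P(t_df > t_crit·√((n − k)/n)).

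| k per arm | df | t_crit | factor | effective cut-off | type I error |
|---|---|---|---|---|---|
| 1 | 16 | 2.120 | √0.9 = 0.949 | 2.011 | 6.1% |
| 2 | 14 | 2.145 | √0.8 = 0.894 | 1.918 | 7.6% |

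**Step 2: the planned layout.** A null simulation used 4 arms of 10, three visits, r = 0.5 or 0.7, and 10% or 20% missing at later visits, with 1,500 runs per scenario (simulation standard error √(0.05 × 0.95/1500) = 0.6 points).
- Two-arm contrast of change to the last visit, least-squares fill with reduced df: 5.5% to 7.9% when data are missing completely at random. The lowest value is within simulation error of 5%. Under dropout that depends on baseline and differs by arm it was 6.6% to 10.0%, with bias of 0.06 to 0.16 SD.
- Baseline-adjusted mixed model on observed data: 4.4% to 5.1% throughout, with bias of at most 0.03 SD.
- Four-arm group-by-time F test with least-squares fill: 7.7% to 8.4% at 10% missing completely at random. Across scenarios an arm-mean fill gave 5.4% to 11.6%, and carrying the last value forward 1.1% to 3.3%.

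The error rate therefore depends on a fill method that the article leaves open.

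**Step 3: precision with complete data.** In units of the APCI variance, change from baseline has variance 2(1 − r) and the baseline-adjusted outcome 1 − r². Their ratio is (1 + r)/2. Power is Φ(d/√(2v/n) − 1.96), with v the variance in the table, d = 0.57 (the lower end of the article's range) and n = 10 per arm.

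| r | change | adjusted | ratio | reduction | power, change | power, adjusted |
|---|---|---|---|---|---|---|
| 0.5 | 1.00 | 0.75 | 0.75 | 25% | 24.7% | 31.3% |
| 0.7 | 0.60 | 0.51 | 0.85 | 15% | 37.7% | 43.0% |
| 0.9 | 0.20 | 0.19 | 0.95 | 5% | 81.3% | 83.2% |

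Estimating the slope with 40 dyads costs about 3% of the variance (ratios 0.77, 0.88 and 0.98), so at r = 0.9 little of the gain is left.

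**The case against.** Several stronger readings are tempting, and the article does not support them.

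- **That the stated method inflates type I error.** No method is stated. Single filling is an inference, though a natural one, and carrying the last value forward is conservative. Naming the method may also be left to an analysis plan that is not shown. What stands is that the remedy the article does write down, lowering df, does not protect the level for mean or least-squares fills. The 20% scenarios also lie beyond the article's own ceiling.
- **That baseline as an outcome level makes the test wrong.** In a randomised comparison with complete data the group-by-time test is valid; the cost is precision. A group main effect over three visits would capture only two thirds of a constant later effect, but the article never makes that main effect its target.
- **That no primary model can be identified.** The split-plot ANOVA is introduced as the effect analysis and the mixed models follow for another purpose, so the order is readable.
- **That the assumption tests do harm.** The article says "A Mauchly test will be calculated for each variable to ensure the assumption of sphericity", and no test can ensure an assumption. With 4 arms of 10 and mild non-sphericity (epsilon about 0.86 to 0.88), Mauchly's test detects the departure only about half the time. The consequence is small: group-by-time type I error is 5.3% to 5.4% if a Greenhouse-Geisser correction follows a significant test (an assumption, as none is stated), and 6.0% to 6.1% with no correction at all. Box's test was not evaluated.
- **That the replacement is valid without conditions.** It needs data missing at random and a reasonable covariance model. The Study design section describes paired randomisation and sessions delivered to groups of dyads. A model with covariance within dyads only ignores both, and the simulation above assumed independent dyads.

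**Conclusion.** The point holds in limited form. If missing values are filled singly by arm mean, the level is about 6.1% at the protocol's own dropout ceiling and 7.6% at twice that loss. Least-squares fills in the full layout mostly give similar or larger excesses, while some other fills err the other way. Separately, adjusting for baseline instead of comparing changes would lower residual variance by 25% to 5% for r from 0.5 to 0.9, worth about 7 to 2 points of power at d = 0.57. These sizes rest on equal arms of 10, equal variances, an assumed r and an assumed fill. This is a worthwhile improvement to the analysis; it does not show that the planned test is invalid with complete data.

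**What to change.** Make the already planned mixed model the primary APCI analysis:
- post-intervention and follow-up APCI as outcomes;
- baseline APCI, arm, visit and arm-by-visit as fixed effects;
- a within-dyad covariance and small-sample degrees of freedom (for example Kenward-Roger);
- all randomised dyads with any later visit, analysed as allocated.

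Replace the estimate-and-lower-df sentence with likelihood-based use of the observed data. State that this is valid under missing at random. Account for the randomisation pairs and the session groups where the data allow. Keep the split-plot ANOVA as a sensitivity analysis; dropping the Mauchly and Box tests is optional.

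The cost is a change of wording and a little more analysis work. The article already plans updates to the protocol and names SPSS, which fits such models. The downside is reliance on missing at random, which data missing for unobserved reasons would break; a sensitivity analysis would be needed for that case.
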